## Abstract

**Introduction:**

Multiple sclerosis (MS) causes a progressive disability, which substantially impacts the quality of life (QoL). Health interventions that meet the needs and demands of people with MS are essential to minimize QoL impairment. Expert patient programs (EPPs) facilitate health-related empowerment through peer learning. Based on a previous focus group study, we designed an EPP for MS coordinated by nursing professionals for implementation in the different MS reference units of Catalonia (Southwestern Europe). This study aims to evaluate the effects on quality of life, disease-related knowledge, and self-management related to the health process of the participants of the Expert Patient Program Catalonia™ for people with multiple sclerosis (EPPC-MS).

**Methods:**

Pre-post intervention multicenter clinical study involving 12 groups of 12 participants: six groups including relapsing and six groups including progressive MS patients, with 144 participants from 7 MS reference units from all over Catalonia, organized in six teams. The intervention will consist of nine telematic learning peer-led sessions (one weekly session). The expert patient (EP) leading the sessions will be an individual with MS with disease-related knowledge, who will be further trained by nurses to lead the sessions. Study variables will be measured before and immediately after the intervention and 6 and 12 months after the end of the sessions and will include: QoL, emotional impact, activation of the person, MS-related knowledge, fatigue, habits and lifestyles, health services use, and program-related experience. Baseline characteristics considered will be sociodemographic data, date of MS diagnosis and type, family history, and treatment characteristics. Variables related to disease follow-up will be new relapses and characteristics and changes in the ongoing treatment. The number of sessions attended will also be collected. Study variables will be analyzed using a pre-post comparison.

**Discussion:**

Peer-led learning programs led by EP help empower people with chronic conditions and offer them tools to improve their autonomy and QoL. This study’s intervention will be performed remotely, offering advantages both for people with chronic conditions and the healthcare system regarding the facilitation of family and work conciliation, saving time, simplifying attendance to meetings, lowering costs, and using fewer material resources.

**Trial registration:**

NCT04988880 on September 22, 2021.

## Introduction

Multiple sclerosis (MS) is a chronic autoimmune degenerative disorder of the central nervous system with a variable clinical course characterized by a progressive disability, causing a substantial impact on quality of life (QoL) (1). Identifying and solving the needs and demands of individuals with MS is fundamental to minimizing their QoL impairment and improving their well-being (1). However, the needs and demands related to MS diagnosis and evolution generate a dynamic and complex scenario, requiring an individualized and high-quality healthcare planning focused on solving these needs (2). In this regard, patient-centered healthcare systems are more cost-effective and improve health literacy and patient participation (3). In addition, it is necessary to simultaneously incorporate a positive view of health that promotes individuals’ empowerment to solve health challenges (2).

Expert patient programs (EPPs) facilitate patient-centered healthcare delivery by improving individuals’ understanding of chronic diseases through knowledge transfer and exchange, thus promoting autonomy and self-care through a proactive approach, improving health indicators and reducing the use of healthcare resources (4). In addition, they facilitate the empowerment of people with MS and improve their well-being and overall perception of health (5, 6), enabling them to reorient their priorities, plan their activities, and choose their care and health preferences (7).

An Expert Patient Program of Catalonia™ (EPPC), consisting of a peer-led learning intervention, was included in the Health Plan of Catalonia 2011–2015 (Spain) and maintained in subsequent plans. The EPPC focused on self-responsibility, self-care, and promotion of people’s autonomy (8, 9). The Expert Patient (EP), a non-healthcare professional with the same chronic condition, leads the program sessions, developed in groups of 10–12 participants with the same long-term condition, guided by a nurse (4). EPs are people with significant knowledge of their disease and treatment in addition to self-management skills, who take responsibility for self-care and disease management, know how to identify and respond properly to symptoms, and acquire skills enabling them to manage the impact of the disease, resulting in improved QoL (10). The EPPC complements other health interventions led by healthcare professionals and is not currently implemented for the MS population.

In Catalonia, which has a population of over 7 million, more than 10,000 people have MS, of which almost 7,000 are women (11). A previous qualitative study based on focus groups including people with MS allowed to identify the topics to be addressed in the sessions, the ideal profile of the EP and the participants, the program’s design, and the potential benefits of a specific Multiple Sclerosis Expert Patient Program of Catalonia (EPPC-MS) (12). As a result of this pivotal study, the research team defined the final design and contents of the EPPC-MS, which will be implemented across the Catalan territory and remains to be evaluated for its ability to improve the empowerment and QoL of people with MS.

## Objectives

The primary objective of this study is to deploy the EPPC-MS across Catalonia. Secondary objectives are to evaluate the effectiveness of the EPPC-MS in reducing the emotional impact of MS and improving QoL, fatigue management, patient activation, habits and lifestyles, and MS knowledge of participants after completing the program. Additional secondary objectives are to evaluate the effectiveness of EPPC-MS in improving health outcomes according to the type of MS, the use of healthcare services by participants, the satisfaction of the EP and the participants with the EPPC-MS, and the long-term persistence of program benefits (at 6 and 12 months).

## Methods

### Overall study design

This research will be conducted using a pre-post intervention multicenter clinical study design to evaluate the territorial implementation of a specific EPPC-MS for people with MS. The study is planned for development during a period of 36 months (January 2021–December 2023). The common goal of this kind of study is to find whether a health intervention affects the participants and their clinical variables and health-related outcomes (13). The intervention sessions will be conducted remotely using Microsoft Teams platform to avoid face-to-face meetings during the current pandemic situation (SARS-CoV-2) as part of a risk mitigation strategy (14). EPPC managers will provide this platform linked to the Health Department of Catalonia, who will endorse its use. Each intervention will consist of nine weekly sessions, lasting an average of 3 months.

This study protocol adheres to the Standard Protocol Items: recommendations for Interventional Trials (SPIRIT) guidelines^1^ for reporting study protocols.

### Study setting

The Catalan healthcare system provides free and universal healthcare to its over 7 million population. The estimated 10,000 individuals who live with MS in Catalonia receive care in multidisciplinary reference MS units. The study will be carried by six teams from 7 MS units located across Catalonia: one from Girona, three from Barcelona, one from Lleida, and two from the Tarragona area (Tarragona unit and Reus unit) pariticipating as a joint team (Figure 1). The participating MS units are the main multidisciplinary reference units of the territory for individuals diagnosed or suspected of demyelinating disease and specifically MS. The study will start after the approval of each local Clinical Research Ethics Committee.

**Figure 1 fig1:**
[figure not shown]
Location of the seven participating multiple sclerosis units. The line between the hospital in Tarragona and the hospital in Reus indicates that these 2 units will participate as a joint team, resulting in total of six participating teams.

### Participant and unit timeline

Each unit will identify and recruit two groups of people with two forms of MS: one group of people with relapsing MS and one with progressive MS, resulting in a total of 12 groups. The program will be implemented in four consecutive phases, including three groups of participants from 3 MS units per phase that will undergo the 9-week intervention simultaneously. After completing the intervention in Phase 1, the same 3 units will start Phase 2 with the remaining three groups in any order (e.g., first the relapsing group and then the progressive one). Hence, 3 MS units will participate in the first two phases. Immediately after the first two phases are completed, the three remaining units will start the intervention in their groups in Phase 3 and, after completing the three groups, in Phase 4. Each group will be invited to attend a follow-up session 6 and 12 months after the end of the intervention to share any changes on their daily habits resulting from the learning program, and the application of disease management strategies (see Figure 2).

**Figure 2 fig2:**
[figure not shown]
Flow diagram and timeline of participants. BICAMS, Brief International Cognitive Assessment for Multiple Sclerosis; HADS, Hospital Anxiety and Depression Scale; M, month; MS, multiple sclerosis. *Participant candidates with BICAMS and HADS data obtained in the routine neurorehabilitation screening will not be required to sign an informed consent for the screening procedure, only to participate in the study.

### Selection of participants and EPs

Patients with a diagnosis of MS treated in the participating MS units will be eligible to participate as participants or EPs in the deployment of the EPPC-MS. All members of the MS multidisciplinary teams will identify participant and EP candidates according to their criteria based on their MS-related knowledge and ability for self-care and self-management, and will invite them to participate. The teams coordinate the process of selection and assessment of participants’ inclusion criteria, including a visit with a trained neuropsychologist to administer the Brief International Cognitive Assessment for Multiple Sclerosis (BICAMS) (15) and Hospital Anxiety and Depression Scales (HADS) (16). Furthermore, the teams initiate and coordinate all the steps for the selection of EPs among pre-selected candidates. A nurse [i.e., the study’s principal investigator (PI)] will coordinate and provide support for these processes to the participating MS units, and will monitor the process to ensure protocol compliance.

Eligible participants must meet the following inclusion criteria: (1) be ≥18 years old; (2) have reported the need for support for disease self-management or to improve MS-related knowledge; (3) confirm availability to attend at least 80% of the sessions; (4) sign an informed consent. Patients meeting any of the following exclusion criteria will not be eligible: (1) be unable to speak or write in Spanish or Catalan; (2) have aphasia or an auditory disorder preventing them from interacting with the group; (3) have a severe cognitive impairment, defined as a score of 1.5-fold the standard deviation below the population mean in one of the three subtests of the Spanish version of the BICAMS (15); (4) have severe emotional impairment, defined as a score above 11/21 on any of the two Hospital Anxiety and Depression Scale (HADS) subscales (anxiety and depression) (16); and (5) have any psychopathological comorbidity or mental disorder diagnosis that may restrict their interaction with the group.

To be eligible as EPs, individuals must meet the same inclusion criteria as participants. However, they must lack the need for support for disease self-management and should have MS-related knowledge. Healthcare or educational professionals and individuals meeting participants’ exclusion criteria will be ineligible as EPs. Furthermore, EPs are selected among patients diagnosed before 2018 to ensure sufficient disease-related knowledge based on their own experience and interactions with the health care system and professionals. Additionally, EPs are selected among patients showing the ability for self-management and self-care and those with a positive perception of the disease. No objective instrument or scale will be used to assess EP inclusion criteria. However, health care professionals from the MS units follow patients closely, getting to know them and, therefore, can appraise the patients’ characteristics and skills. Furthermore, the selection of patients diagnosed before 2018 ensures a long-term relationship with the multidisciplinary teams. Irrespective of these criteria, potential EP candidates could meet other characteristics, such as information and communication technologies skills, communication and leadership skills, and comprehensive experience and knowledge of the health process. The information and communication technologies skills are partly appraised during contacts with the MS units using electronic communication tools, such as email or other platforms, and by evaluating the use of reference information websites. During the selection process, EPs are informed that their participation will be altruistic and should expect no compensation.

Each of the participating teams will select three EP candidates, who will be scheduled for interviews with the PI and the institutional managers of the EPPC to further assess their adequacy to fulfill the EP role. Disease-related knowledge will be assessed using questions from the disease knowledge, habits and lifestyle, and quality of life questionnaires used to evaluate the program, and candidates will be engaged to speak about self-management, self-care, and their future role as EP to assess their predisposition, leadership skills, and communication abilities. This strategy for EP selection has been used previously in other versions of the program (17). Moreover, the interviews will be conducted remotely using the same platform that will be used for the program sessions to confirm the ability of the EP candidates to use it. The PI and EPPC managers will select one EP per team, who will be provided with the session materials and will be trained for their role. The training sessions will allow us to confirm the adequacy of the EPs and, if necessary, the selection may be reconsidered.

### Sample size

Sample size is estimated based on the deployment of the EPPC-MS across Catalonia (primary outcome). Sample size was calculated by prioritizing those units willing to participate in the study and interested in implementing the program in the future to offer it to the people with MS followed up at the unit regularly. Of the 7 units willing to participate, the 2 units located in the Tarragona area (Tarragona and Reus units) will particpate as joint team, resulting in a total of six participating teams. Each MS team will include two groups of people with MS, of which one group will include people with relapsing MS and the other group people with progressive MS, resulting in a total of 12 groups, with six groups for each MS type. Based on the methodology used in the program, the recruitment target will be 12 people with MS per group (144 individuals in total). We expect this group size will compensate for possible losses during the intervention and ensure a minimum of 8–10 participants per group throughout the program (96–120 participants) (4). We estimated this sample size based on the number of people with MS in Catalonia (⁓10,000) and the number cared for at each of the MS units. Ideally, the exact calculation of the sample size required to assess the study’s secondary outcomes (EPPC-MS effects) should be based on the results of a pilot study testing the program’s effects in a smaller sample of patients. However, this study has not yet been completed. If the 12 groups are insufficient to reach an appropriate sample, the participating investigators will contact the Ethics Committees to request their approval to expand the number of groups.

### Recruitment

Participants: follow-up of people with MS involves therapeutic support by the multidisciplinary team during clinical visits at the unit facilities (i.e., regular follow-up visits), the day care clinic, or through non-scheduled consultations for any reason (i.e., needing additional care due to treatment secondary effects or disease symptoms, information, and support). After completing a routine follow-up visit by a healthcare professional, people with MS self-reporting the need for support for disease management or the need to improve MS-related knowledge will be invited to participate in the study. To ensure that the target sample size is reached, healthcare professionals, members of the MS multidisciplinary teams may actively identify candidates by asking people with MS about their need for additional support and information for disease management. People with MS initially willing to participate will be referred to the study coordinator at each participating center to receive complete information about the study.

Neuropsychologists within the MS multidisciplinary teams will assess the inclusion and exclusion criteria of participant candidates. To assess severe cognitive and emotional impairment (exclusion criteria), a trained and experienced staff in assessing cognitive and emotional impairment will screen participant candidates using the BICAMS (15) and HADS (16) instruments. These tests are part of the routine neurorehabilitation screening procedure, but may be administered to other participant candidates outside the routine screening that require a specific consent. Before the study starts, a senior neuropsychologist will lead an update session for all neuropsychologists of the participant centers to ensure uniformity of data collection (18). Eligible candidates will receive the patient information sheet and be asked to sign a written informed consent before assessing the selection criteria, such as cognitive and emotional impairment (when required). The participant timeline summarizes the recruitment process (Figure 3).

**Figure 3 fig3:**
[figure not shown]
Expert Patient Program timeline. EP, expert patient; EPPC-MS-Relapsing and EPPC-RMS, expert patient group including participants with relapsing multiple sclerosis; EPPC-MS-Progressive and EPPC-PMS, expert patient group including participants with progressive multiple sclerosis; G1 to G12, expert patient groups 1 to 12; M, month.

Expert Patient candidates will be selected among the MS population followed up at each unit and according to the eligibility criteria. The study PI will evaluate the knowledge of EP candidates to confirm their eligibility. Additionally, people with MS who participated as EP in the pilot study testing the program effects or other MS units may be invited to participate again as EPs in this study.

### Intervention

The intervention aims to reinforce positive knowledge concisely using plain language that all participants can understand. Throughout nine 90-min sessions (one per week) led by an EP, participants in the group will share their knowledge and experiences on all aspects of MS and its self-management. The organization of session and its contents are summarized in Table 1.

**Table 1 tab1:** Expert Patient Program Catalonia-Multiple Sclerosis (EPPC-MS): sessions and contents.

Session	Content description
1. Introduction	Presentation of group members, program objectives, session contents, session development, and questionnaires
2. The disease	What is multiple sclerosis? Concept, causes, types of MS, and diagnosis
3. Signs and symptoms	Relapses (relapsing MS), progression (progressive MS), and fatigue
4. Treatment	Existing treatment, future treatments, treatments during pregnancy, and alternative therapies
5. Health promotion	Healthy lifestyles: nutritional facts, activity and exercise, tobacco, vitamin D and sun exposure, and obesity
6. Taboo subjects	Urinary and fecal incontinence, sexuality, and sexual dysfunction
7. Emotional impact and relationships	Coping with the disease, work and family relationships, and available resources for emotional support
8. Social environment and quality of life	Rehabilitation and physical aspects, social resources, and benefits
9. Program finalization	Wrap-up session

The study’s PI is a nurse specialized in MS and will train the EPs and support them throughout the intervention, together with professionals in each of the participating units. Before starting the intervention, the study’s PI will train the EPs in a presentation of all the learning materials and contents of each session. Furthermore, using role-playing activities, the nurse PI will ask example questions related to the contents of each session to the EPs to be answered jointly. The training and activities aim to expand the EPs’ knowledge of the sessions’ contents and gain confidence to lead and answer the questions.

Throughout the intervention, a professional nurse in the MS team and the EP will meet before each session to prepare the contents and solve any doubts from the previous sessions. In all sessions, two nurses, on from the participating team and one member of the EPPC panel of directors, will act as an observers, provide help and support to the EP if needed, and assess each session jointly with the EP at the end.

Sessions are divided into two blocks: a first block with a theoretical introduction to focus on the day’s topic, conducted by the EP (30 min), and a practical block (60 min). A previous pivotal study characterized the topics addressed in the sessions (12). After the first block introducing the topic, the EP will encourage interaction, facilitating the communication of doubts, questions, or experiences related to the contents, which will be solved or answered by participants or collectively through discussion within the group (practical block). This intervention strategy with an EP leading the session and the participation of all the group members aims to empower them to gain control over their health situation. The knowledge acquired will come from the information provided by the EP and the knowledge resulting from the life experiences regarding MS of all the participants involved in the intervention.

Participants will complete questionnaires according to the study schedule (prior and immediately after the intervention, and at the evaluation periods 6 and 12 months after the end of the intervention) to assess the secondary outcomes. The completed questionnaires will be collected at post-intervention sessions (at 6 and 12 months), allowing participants to clarify concepts and expose doubts regarding the contents of the previous nine sessions.

To ensure adherence, the platform will send reminders before each session and, if necessary, sessions will be rescheduled.

### Outcomes

The primary outcome of this study is the deployment and implementation of the EPPC-MS in the participating MS units across Catalonia. The feasibility of the EPPC-MS implementation will be appraised in terms of the correct inclusion of the six participating teams and the successful execution of all the procedures. Participation in the study entails sufficient training of professionals at MS units for the correct identification and recruitment of participants and EPs and for appropriate data collection and monitorization of study procedures. At the end of the study, the participating units will be able to implement the EPPC-MS independently and autonomously based on the methodologies of the EPPC-MS.

Secondary outcomes are those related to the effectiveness of the program and include changes in QoL, measured using the Multiple Sclerosis Quality of Life 54 items (MSQOL-54) questionnaire (19, 20); emotional impact, measured using the HADS (16); fatigue management, measured using the Fatigue Severity Scale (FSS) (21); patient activation and engagement, measured using the 13-item Patient Activation Measure (PAM-13) (22); patient knowledge, measured using the EPPC specific questionnaire about MS-related knowledge; individuals’ habits and lifestyles, measured using the EPPC specific questionnaire about habits and lifestyles; use of healthcare services, such as visits to the MS unit, visits to the general physician (GP), and visits to the accident and emergency (A&E); and Patient Reported Satisfaction (i.e., experience), measured using the EPPC-specific questionnaire about patient-reported experience measures (PREMs), designed *ad hoc* for this study. Except for the latter, we will compare the scores obtained before the intervention and at post-intervention timepoints (immediately after the intervention and at 6 and/or 12 months after the end of the intervention). The participants and the EPs will answer the patient-reported satisfaction questionnaire, and scores will be compared immediately after the intervention and at 6 and 12 months.

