### Study variables and data collection

Data will be collected according to the study timeline depicted in Figure 4. Baseline sociodemographic characteristics of EPs and participants, including age, gender, marital status, family support, educational level, and employment situation, will be collected during the recruitment visit. Disease variables, including, among others, date of diagnosis, type of MS, MS treatment, and disability, will be collected from the clinical records before the intervention (Week 1) and after the intervention (Week 9 and at 6 and 12 months after the end of the intervention). Variables related to the use of healthcare services include the number of visits to the MS unit (both scheduled routine follow-up visits and unscheduled visits), primary care visits, and A&E department visits during 1 year before and after the intervention, and will be collected prior to the intervention (Week 1) and after the intervention (Month 12), respectively, by the research team using a questionnaire. This information is routinely registered during visits to clinics and healthcare consultations. It is made available by the health registry of the region to the healthcare institutions after institutional authorization from the Ethics Committee of each center. Before the study starts, all the healthcare professionals involved will receive an update session led by the study’s PI regarding data entry to ensure uniform data collection (18).

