**Figure 4 fig4:**
[figure not shown]
Assessments and data collection timeline. BICAMS, Brief International Cognitive Assessment for Multiple Sclerosis; EP, expert patient; FSS, Fatigue Severity Scale; HADS, Hospital Anxiety and Depression Scale; MSQoL-54; Multiple Sclerosis Quality of Life-54 items; PAM-13, patient activation measure; PRT, participants; RT, research team.

Patient-reported outcomes (PROs) and PREMs evaluating the impact of the intervention (secondary outcomes) will be assessed using specific instruments (i.e., questionnaires) according to the study timeline (Figure 4). Except for participants and EP experience with the program, which will be evaluated after the intervention, questionnaires will be self-administered prior to the intervention (Weeks 1–3) and after the intervention (Week 9, Month 6, and Month12). Pre-intervention questionnaires will be distributed within the first 3 weeks considering the contents of each session. Hence, questionnaires assessing fatigue and lifestyle will be administered in session 2 (Week 2) and the corresponding contents will be presented in sessions 3 and 5, respectively. The Research Electronic Data Capture (REDCap) platform will automatically send the questionnaires and instructions for completion, and participants will complete them online on the platform’s site. The platform automatically resends the questionnaires weekly during three consecutive weeks in case answers are not received. Moreover, it allows real-time monitoring of the questionnaires received and the PI may resend the questionnaires manually and contact participants to solve any issues regarding questionnaire completion on the platform’s site.

The study’s PI, a nurse, will maintain a field notebook to record the basic information for each session, including participants, the session’s contents, the group, and the MS reference unit. The PI will additionally collect participants’ comments and questions related to the session’s topic and final comments regarding each session development. The EP will answer all questions collected as unanswered during each session in the next. Furthermore, the EP will clarify any inappropriate or inaccurate information shared during sessions in the next session, with the support of the research team.

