### Statistical analysis

Statistical analyses will be performed on the intention-to-treat (ITT) population, defined as the population of patients starting the intervention, irrespective of program completion. Continuous variables will be described as mean and standard deviation (SD) or, in case of non-compliance with normality criteria, median and interquartile range (IQR), and categorical variables as absolute frequency and percentages. The non-parametric U Mann–Whitney test for independent samples and the Wilcoxon test for dependent samples will be used to analyze the relationship between a categorical variable and a continuous variable. The Chi-squared test or the Fisher’s exact test will be used to analyze the relationship between two categorical variables. For the secondary outcomes, changes in the study variables throughout time (i.e., before and after the intervention) will be analyzed using an ANCOVA or linear mixed model to etimate changes in effect size. No methods to handle missing data (i.e., imputation) will be applied. A significance level of 5% will be considered. Data will be analyzed using the latest version of the Statistical Package for the Social Sciences (SPSS) software (IBM, Armonk, New York, United States).

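### Long-term persistence is an objective, but the only comparison clearly named for the effectiveness scores is with baseline, which cannot show how much of the Week 9 gain is kept

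*Protocol article*

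**What the plan says.** The Objectives section lists effectiveness after completing the program and, as an additional secondary objective, "the long-term persistence of program benefits (at 6 and 12 months". It does not say whether persistence means still better than baseline, or no worse than at the end of the program.

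The Outcomes section then fixes the comparisons. For all secondary outcomes but satisfaction: "Except for the latter, we will compare the scores obtained before the intervention and at post-intervention timepoints". The timepoints are given as "immediately after the intervention and at 6 and/or 12 months after the end of the intervention". Satisfaction, which has no pre-program value, is treated differently: "scores will be compared immediately after the intervention and at 6 and 12 months".

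The Statistical analysis section says that "changes in the study variables throughout time (i.e., before and after the intervention) will be analyzed using an ANCOVA or linear mixed model", so its gloss on time is again before against after.

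The Study variables and data collection section schedules the questionnaires before the program and "after the intervention (Week 9, Month 6, and Month12". A Week 9 value therefore exists for them. Healthcare use is different: the yearly counts "will be collected prior to the intervention (Week 1) and after the intervention (Month 12), respectively", so there is no Week 9 value.

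**The concern.** A comparison of Month 12 with baseline has the null hypothesis that no net change remains. Rejecting it is compatible with most of the Week 9 gain having gone. Failing to reject it after a significant Week 9 result does not show that the gain has gone. The question of whether a gain lasts is a question about the change from Week 9 to Month 6 and Month 12. The article applies a comparison across post-program visits to satisfaction only.

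At stake is the conclusion on a stated secondary objective. If the report has only baseline contrasts, its readers are likely to set a Week 9 result beside a Month 12 result and compare significance. A program whose effect has halved could then be described as lasting, and one that keeps a modest effect as faded.

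**Working it through.** **Figures in the article.** 6 teams × 2 groups × 12 people = 144 recruited. With 8–10 people kept per group, 12 × 8 = 96 and 12 × 10 = 120. These match the Sample size section. They are deployment counts. No effect size, SD or power is given for the secondary outcomes, so there is no power figure to reproduce.

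**Inputs.** From the article: n = 96 and 120 (stated for the program period, not for Month 12) and the 5% level. Assumed: two-sided tests, a Week 9 gain *g* of 0.2–0.5 baseline SD, exactly half of it left at Month 12, equal SD at each visit, equal between-visit correlation *r* of 0.5 or 0.7, and no clustering by group.

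**Formula.** The SD of a change between two visits, in units of the score SD, is √(2(1 − r)). This is 1.00 at r = 0.5 and 0.775 at r = 0.7. For Month 12 against baseline, the paired t test has noncentrality λ = (g/2) × √n / √(2(1 − r)). Examples:
- g = 0.3, r = 0.5, n = 96: λ = 0.15 × 9.80 / 1.00 = 1.47, power 31%.
- g = 0.5, r = 0.7, n = 120: λ = 0.25 × 10.95 / 0.775 = 3.54, power 94%.

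Chance that Month 12 differs significantly from baseline when half the gain is lost:

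| Week 9 gain | r 0.5, n 96 | r 0.5, n 120 | r 0.7, n 96 | r 0.7, n 120 |
|---|---|---|---|---|
| 0.2 SD | 16% | 19% | 24% | 29% |
| 0.3 SD | 31% | 37% | 47% | 56% |
| 0.4 SD | 49% | 58% | 71% | 80% |
| 0.5 SD | 68% | 78% | 88% | 94% |

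**Both visits significant.** Simulation of three correlated visits (at least 4,000 trials per scenario, so good to about a percentage point) gives about 13–27% at 0.2 SD, 30–56% at 0.3 SD, 49–80% at 0.4 SD and 68–94% at 0.5 SD.

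**The opposite error.** For a half-lost 0.3 SD gain, Week 9 is significant and Month 12 is not in about 44–55% of trials. For a fully kept 0.25 SD gain, the same pattern appears in about 4–15%.

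**What the direct contrast adds.** When half is lost, the mean change from Week 9 to Month 12 is −g/2. With equal correlations its λ has the same size, so the table also gives the chance that this contrast detects the loss. That is modest at 0.3 SD, so the contrast is better used as an estimate with an interval than as another test. The half-width of its 95% interval is t × √(2(1 − r)) / √n. At r = 0.5 this is 0.20 SD (n = 96) or 0.18 SD (n = 120), and at r = 0.7 it is 0.16 or 0.14 SD. For a 0.5 SD gain that has halved, with r = 0.5 and n = 96, the expected interval is −0.25 ± 0.20, or −0.45 to −0.05 SD. A baseline contrast alone does not supply that statement.

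**Clustering.** With an intraclass correlation of 0.05 on change, the design effect is 1 + 7 × 0.05 = 1.35 for 8 per group and 1 + 9 × 0.05 = 1.45 for 10. At r = 0.5, the 68% and 78% for a 0.5 SD gain fall to about 55% and 61%.

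**The case against.** Four points can be made for the plan as written.

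- No decision rule is stated. A reader might infer that persistence will be declared when two p-values fall below 5%, or loss when the second does not. Neither rule is in the article. The Statistical analysis section speaks of estimating change, so estimates at each visit could be read side by side. This stands: it is too strong to say that persistence is judged only by significance against baseline.
- Still being better than baseline at 12 months is a legitimate, weaker meaning of persistence, particularly in a pre-post implementation study that disclaims causal aims. This stands too. The comparison is not a wrong test. The difficulty is that the objective does not choose this meaning, and the comparison answers only this one.
- A reader might infer that a half-lost gain would usually be reported as persistent. The article gives no effect size, and the figures support that only for gains of about 0.4–0.5 SD or more. For smaller gains the likelier misreading is that the benefit has gone.
- Lists of contrasts commonly belong in an analysis plan, which is not shown, and a mixed model could supply them. This limits the point but does not remove it. The article does more than stay silent: it names a baseline comparison for these scores and a different one for satisfaction.

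**Conclusion.** The point holds in a limited form. Persistence is an undefined objective, and the only comparison clearly named for the effectiveness scores shows whether some benefit remains, not how much of the Week 9 gain is kept. The data to estimate the latter are already collected for the questionnaires. The point does not extend to healthcare use, for which only the year before and the year after can be compared.

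How often the baseline contrast would mislead depends on the true gain, which the article does not give. The percentages under the working also assume that 96–120 people are still observed at Month 12. Fewer people or clustering would make a significant Month 12 result less likely, and so shift the risk towards a false reading of loss. This is a worthwhile improvement to a secondary analysis and does not call the design into question.

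**What to change.** In the Outcomes and Statistical analysis sections:

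1. For the questionnaire outcomes measured at Week 9, Month 6 and Month 12, commit to the linear mixed model option, with all four visits in one model.
2. Report Month 6 minus Week 9 and Month 12 minus Week 9 with 95% confidence intervals, beside the contrasts with baseline.
3. Describe persistence from these estimates together. Keep Month 12 against baseline as the net change, and state that a non-significant result there will not be read as loss of benefit.
4. Leave healthcare use on its before-and-after-year comparison.

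A fixed retention threshold, such as requiring more than half the gain to be kept, is not needed. Nothing in the article supports a particular fraction, and for a fully kept 0.25 SD gain that rule would succeed in only about 30–53% of trials.

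The cost is two extra contrasts per outcome, a few sentences, and giving up the choice of an ANCOVA on a single follow-up score, which does not supply these contrasts. No new visits or data are needed.
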